### Endpoints of Safety

Endpoints of safety are

• Death caused by suicide

• Suicide attempt

• Suicidal crisis (explicit plan for serious suicidal activity without suicide attempt) as defined in Calgary Depression Rating Scale for Schizophrenia [CDSS; [27]], item 8, rating 2)

• Severe symptomatic exacerbation, defined by the Clinical Global Impression Scale (CGI) which includes ratings of illness severity, changes in overall clinical status, and therapeutic effects. A rating of CGI2 ≥ 6 and CGI 1≥ 6 would be regarded as severe adverse event.

Information about these safety parameters is recorded in the CRF every four weeks by the study rater as part of the regular clinical assessment.

### Secondary Endpoints

A complete overview over the endpoints of this trial is given in Table 2. Secondary endpoints will cover additional aspects of outcome, such as the course of symptoms and insight into the disorder. Results regarding secondary outcomes will only be interpreted as exploratorily. In particular, PSYRATS [28] provides information about the distress caused by symptoms, AMDP [29] provides additional information about the content of delusions, and SUMD [30] allows for a more detailed analysis of the patient's self awareness regarding symptoms, i.e. insight.

**Table 2 T2:** Timing of assessments of endpoints for safety and efficacy

	T0	T1,2	T3	T4,5	T6	T7,8	T9	F1	F2	F3	F4
	**pre**	**treatment phase** **(monthly assessments)**					**post**	**follow-up** **(every 6 months)**			

**Month**	**0**	**1,2**	**3**	**4,5**	**6**	**7,8**	**9**	**15**	**21**	**27**	**33**

***Inclusion Assessment***											

Structured Clinical Interview for DSM-IV	x										

Anamnestic interview	x										

***Safety***											

Severe Adverse Event asessment^1^		x	x	x	x	x	x	x	x	x	x

CDSS [27]	x	x	x	x	x	x	x	x	x	x	x

Clincal Global Impression (CGI)		x	x	x	x	x	x	x	x	x	x

***Efficacy***											

PANSS [22]	x	x	x	x	x	x	x	x	x	x	x

PSYRATS [28]	x	x	x	x	x	x	x	x	x	x	x

GAF and Social Status	x	x	x	x	x	x	x	x	x	x	x

Blindness Protocol	x	x	x	x	x	x	x	x	x	x	x

CSSRI^3 ^[61]	x		x		x		x	x	x	x	x

EQ-5D [64]	x		x		x		x	x	x	x	x

SUMD [30]	x						x		x		x

AMDP-psychosis items^2 ^[29]	x						x		x		x

Side effect rating scale [65]	x						x		x		

SCL-90-R [31]	x						x		x		x

FSKN [33]	x						x		x		x

Neuropsychological test battery	x						x				

^1^Suicide, Suicide attempts, ^2 ^items 33-58, ^3^includes assessment of medication and medication compliance; CDSS: Calgary Depression Scale for Schizophrenia; PANSS: Positive and Negative Syndrome Scale; PSYRATS: Psychotic Symptom Rating Scales; GAF: Global Assessment of Functioning; CSSRI: Client Sociodemographic and Service Receipt Inventory; EQ-5D: Euro Quality of Life - 5 Dimensions; SUMD: Scale to Assess Unawareness of Mental Disorder; SCL: Symptom Check List; FSKN: Frankfurter Selbstkonzeptskalen (Frankfurt Self-Concept Scales)

Treatment effects in the field of psychiatric disorders should always be assessed also from the viewpoint of the patient. However, a disorder of self evaluation is part of the positive syndrome which is the reason for choosing observer ratings as primary endpoint. On the other hand, the general rating of patients about their symptoms is important and is represented by the following secondary endpoint.

The Symptom Checklist [SCL-90-R; [31]] assesses subjectively felt impairments due to somatic and psychic symptoms within a frame of seven days. The SCL-90-R for example also assesses psychotic or depressive symptoms. Thus, self ratings of these symptom dimensions seem to be a sensible completion of symptom ratings. As CBT is supposed to reduce symptoms we hypothesize, that SCL-scores will be lower in CBT compared to ST at T9.

Low self-esteem might be viewed as a product of the schizophrenic patient's experience of positive as well as negative symptoms and its deleterious social consequences [32]. On this background, the self concepts as measured by the Frankfurt Self-Concept Scales [FSKN, [33]] will be assessed. The subscales of this self rating questionnaire assess attitudes towards the own person (e.g. self esteem). Cognitive behavioural therapy might have a beneficial impact on self-esteem in schizophrenic patients [32]. Since self concepts do usually change slowly the FSKN will only be applied at baseline, post-treatment, 6-month follow-up, and 12-month follow-up.

Traditional instruments that measure self-esteem may not relate directly to the schema construct as outlined in recent cognitive models. The Brief Core Schema Scales [BCSS; [34]] aim to provide a theoretically coherent self-report assessment of schemata concerning self and others in psychosis. The scales assess four dimensions of self and other evaluation: negative-self, positive-self, negative-other, positive-other. The BCSS will be applied at the same assessment points as the FSKN.

### Quality control/Monitoring

As an instrument for quality control and quality assurance the clinical trial will be monitored. Monitoring will be performed by the Coordination Centre for Clinical Trials at University Hospital Tuebingen (CenTrial) according existing standard operating procedures (SOPs). The purposes of the monitoring are to verify that the rights and well-being of the subjects are protected, that the reported trial data are accurate, complete, and verifiable from source documents, and that the conduct of the trial is in compliance with the study protocol/amendments, with GCP, and with applicable regulatory requirements. The extent and nature of the monitoring will be determined in a monitoring manual before starting the trial. For every on-site visit a monitoring report will be submitted to the sponsor. Status reports of the monitor will inform the sponsor regularly about the actual status in the trial sites.

### Data Management

Case report forms must be completed according to the following schedule:

a) Before the treatment starts: the patient must be screened/randomised at CenTrial. For that purpose all relevant data must be reported.

b) Documentation of the treatment and follow-up visits: Each visit should be documented immediately.

c) Upon occurrence of a Severe Adverse Event (SAE)

All SAEs occurring during the observation period of 9 months must be reported by fax to the sponsor's medical expert, the medical director of the Department of Psychiatry and Psychotherapy of the University of Tuebingen. All forms must be dated and signed by the responsible investigator or one of his/her authorized staff members.

This study is designed to be documented mainly via internet. The study software *koordobas*, an Oracle-based application of the IMB, will be used for the data management. This application was in full compliance with GCP-requirements (e.g. audit trail, validation) at the start of the trial. The eCRF data are reported by authorized investigators via internet on the specific case report forms (eCRFs). The case report forms (eCRFs) must be completed, dated and signed electronically by the investigator or one of his/her authorized staff members as soon as the requested information is available. The list of staff members authorized to sign case report forms (with a sample of their signature) have been sent to CenTrial by the responsible investigators before the start of the study.

In all cases, it remains the responsibility of the investigator to check that case report forms are completely and correctly filled in. The data manager will perform extensive consistency checks on the eCRFs and issue Query Forms in case of inconsistent data. Those Query Forms must be immediately answered and signed by the investigator (or an authorized staff member). The original must be returned to CenTrial and a copy must be appended to the investigator's copy of the eCRFs.

If an investigator (or an authorized staff member) needs to modify an eCRF after the original eCRF has been filled in and returned, he/she can change it by notifying the Data Centre electronically appending a print out of the notification to his own copy of the eCRFs. All modifications will be protocolled by the audit trail of the study software.

All study related data (electronic as well as on paper) will be stored for 10 years in the archive of the Department of Psychiatry and Psychotherapy, University of Tuebingen.

The audio tapes of therapy sessions will be stored in locked filing cabinets. They are to be labeled with the patients ID only. Access to the audio tapes is permitted only with written permission of the principal investigator. The audio tapes will be destroyed after finishing the data analysis.

Assessment, storing, processing, and deleting of person related data will be conducted in accordance to German law.

### Sample size calculation

The primary endpoint analysis will be conducted with linear mixed models (LMM, [35]). As software for sample size calculation for the analysis of longitudinal data using multilevel mixed models is not available, we calculated the sample size for classical ANOVA using nQuery 4.0.

The power calculation is based on published results about CBT for persistent positive symptoms. For the comparison between CBT and TAU Tarrier et al. [36] reported Effect Sizes (ES: (mean_TAU_-mean_CBT_)/SD_TAU_) of 0.33-0.66 for the 18 month follow-up. Tarrier et al. (1998) found an ES of 0.48, Kuipers et al. [37] an ES of 0.6, and Sensky et al. [19] an ES of 0.5. In a review Gould et al. [38] found a range of ES from 0.2 to 1.26. The reported variance differs to a great extent indicating considerable differences with regard to samples or treatments. A recent effect size analysis applied broader inclusion criteria for studies and resulted in an ES of .57 for acute patients (post-treatment analysis) and an ES of 0.27 in chronic patients [3]. These reviews show considerable efficacy of CBT when compared to treatment as usual. However, this study focuses on the difference between CBT and Supportive Treatment (ST). Unfortunately, the power calculation is more difficult for this comparison as fewer studies are available. According to a review of Tarrier et al. [36] the following studies have included ST-control groups: Tarrier et al. [18], Haddock et al. [28], Pinto et al. [39], Lewis et al. [40], and Durham et al. [41]. The effect sizes vary between -.49 in a study including only 21 patients [28] and .99 in a study with 37 patients [39]. In addition, sample characteristics and endpoints are different between the studies. Thus, it does not seem possible to make assumptions about the ES for the comparison between CBT and ST based on the literature.

Regarding drop out rates there is also much heterogeneity with a range between 0% and 36% [36,38]. The majority of studies reports drop out rates of less than 20%. As measures of quality control will be applied and monetary incentives for participation in the follow-up examinations will be offered we expect a drop out rate of about 20%.

On this background we aim to identify an effect size of more than .35 as significant given an anticipated drop out rate of 20%. An ES of .35 would be obtained if the PANSS Scores (Positive Syndrome) at the post treatment assessment were 12 for CBT and 14.5 for ST with a standard deviation of 7.14. An ES of less than .35 would be of limited clinical relevance.

This results in n = 130 per group for a power of 80% and a two-sided significance level of 5% (sample size calculated by nQuery 4.0, Panel MGT0). The confirmatory statistical analysis will be based on the intention-to-treat principle. Patients with missing PANSS-scores at T9 (post-treatment) will be included with the last observation carried forward (LOCF). In case of missing PANSS-scores at T9 the treatment effect will presumably be underestimated by using LOCF. To compensate for this underestimation the sample size should be adapted for drop out. Thus, we plan to include 330 patients (165 per study condition).

As assumptions about the real effect size cannot be based upon the literature we calculated different scenarios: in case of a lower effect size and/or drop out of more than 20% the statistical power will be reduced. For example, a reduced ES of 0.2 would result in a power of only 36% for the drop out of 20%. An increased drop out of 30%would reduce the power to 74% for the minimum ES of .35. On the other hand, a more favourable ES of 0.45 would increase the power to 85% for the maximum drop-out rate of 20%.

With a sample size of 330 individuals (165 each therapy group), ten assessments per patient, one primary analysis variable (therapy) and one covariable (center), the power should also be sufficient for a Mixed Model [42].

Table 3 gives an overview over the number of patients required in the different stages of the trial and the required effort for treatment and assessment. In order to successfully include 330 patients 6 study centers have been included which were committed to participate actively in this trial.

**Table 3 T3:** number of patients required in the different stages of the trial

	total	per center
required number of eligible patients (with 75% refusal)	1304	217
number of patients to be included (incl. 20% drop out)	330	55
number of patients to be analysed (ITT, LOCF)	330	55
number of patients to be analysed per protocol	260	44
treatment sessions (CBT and ST)	5530	922
number of visits	4620	770

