### Statistical Analysis

The primary endpoint for the biometrical evaluation (responsible statistician: CM) is the PANSS-Positive-Score of the Positive and Negative Syndrome Scale at the time of 9 months after inclusion. It will be analysed after completion of T9-assessments.

The statistical hypothesis for the confirmatory test of the primary endpoint is that the treatment groups are significantly different when analysed using multilevel linear mixed models with treatment and study centres as levels of analysis and adjustment for baseline values. The decision for maintaining or rejecting the null hypothesis will be made applying a two-sided test with α = 0.05. A two-sided test will be chosen as the published results about the comparison of CBT and ST are inconsistent. The observed effects will be described by use of means including the appropriate (one-sided) 95%-confidence intervals.

The confirmatory statistical evaluation of the efficacy of the CBT in this trial will be restricted to the primary endpoint. Only the rejection of the null hypothesis will be interpreted as statistical evidence for the efficacy of CBT. The confirmatory statistical analysis will be based on the intention-to-treat principle (ITT). In addition, a "per protocol" (PP) analysis will be conducted

All secondary endpoints will be compared and statistically assessed for descriptive purposes and not in a confirmatory sense. The aim of the analysis is explorative data analysis, not hypothesis testing or generation of evidence for efficacy. Because of the explorative character of this part of the analysis, no a priori statistical analysis plan exists. If adequate, secondary endpoints will be compared and statistically assessed using covariance techniques with baseline values and centers as covariates. Changes of scores over time will be modeled using linear or non-linear or nonparametric models as adequate. In addition, appropriate statistical methods of explorative data analysis including graphical methods and descriptive statistics will be used. No interim analysis and no subgroup analyses are planned.

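### Confirmatory test fills missing T9 PANSS scores by LOCF although monthly ratings and a mixed model are planned; the claim that this only underestimates the effect does not hold in general

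*Protocol article*

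**What the plan says.** All references are to the protocol article.

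- **Missing-data rule** (Sample size calculation): "Patients with missing PANSS-scores at T9 (post-treatment) will be included with the last observation carried forward (LOCF"). The same section ties it to the confirmatory test: "The confirmatory statistical analysis will be based on the intention-to-treat principle". Table 3 repeats the rule for all 330 patients: "number of patients to be analysed (ITT, LOCF").
- **Justification** (same section): "In case of missing PANSS-scores at T9 the treatment effect will presumably be underestimated by using LOCF". The only remedy offered is to raise the sample from 130 to 165 per arm.
- **Model, first description** (Sample size calculation): "The primary endpoint analysis will be conducted with linear mixed models". The section refers to longitudinal data and argues that power suffices with "ten assessments per patient, one primary analysis variable (therapy) and one covariable (center").
- **Model, second description** (Statistical Analysis): "multilevel linear mixed models with treatment and study centres as levels of analysis and adjustment for baseline values". Time or visit is not mentioned.
- **Data available** (Table 2): PANSS at T0, at each month from T1 to T8, and at T9.
- **Other analyses of this endpoint**: a per-protocol analysis only.

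**The concern.** LOCF treats a score from any month between 0 and 8 as an observed month-9 score. If scores move over time, a patient who leaves early is credited with less change than he or she would have had by T9. When this happens to the same extent in both arms, the difference between arms shrinks. When one arm loses more patients, or loses them earlier, that arm looks worse for a reason unrelated to treatment. More dropout in ST would then favour CBT.

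The protocol recognises only the shrinkage and answers it with more patients. A larger sample reduces random error but leaves a bias where it is, and makes a false difference easier to declare significant. This matters because the Statistical Analysis section takes rejection of this one null hypothesis as the evidence for efficacy, and about 20% of patients are expected to drop out.

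The rule is also avoidable. A likelihood-based model fitted to the monthly scores uses every observed visit without imputation. If instead the confirmatory model is a single-time-point model at T9, the monthly ratings enter it only as carried-forward values.

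**Working it through.** **1. The protocol's own figure.** ES = (14.5 - 12)/7.14 = 0.35. At two-sided 5%, the noncentral t gives power 0.803 for 130 per arm, so the stated n reproduces. 130/0.8 = 162.5, or 163, against the stated 165.

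**2. Inputs for the bias check.**
- From the protocol: 165 per arm, SD 7.14, overall dropout 20%, visits T0 to T9, baseline adjustment.
- Assumed, because the protocol gives no figure: linear improvement of 2.5 to 5 points over 9 months, within-patient correlation 0.6, the split of dropout between arms, its timing, and dropout unrelated to outcome within each arm. SD 5 is shown as an alternative.
- Points are on the scale of the sample size section (12 against 14.5). The Primary Endpoint section defines the score as a mean of seven items; on that scale shifts are divided by 7 and error rates do not change.

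**3. Formula with no true difference.**
False shift = (dropout in ST - dropout in CBT) x improvement x mean share of the 9-month course lost.
- Last visit spread evenly over T0 to T8: mean share = 5/9 = 0.556.
- Last visit spread evenly over T0 to T5 (early dropout): mean share = 6.5/9 = 0.722.

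Standard error of the baseline-adjusted difference = SD x sqrt((2/165) x (1 - 0.6²)) = 0.629 for SD 7.14 and 0.440 for SD 5.
Type I error = Φ(-1.96 + shift/SE) + Φ(-1.96 - shift/SE).

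Example: 0.10 x 4 x 0.556 = 0.222; 0.222/0.629 = 0.353; Φ(-1.607) + Φ(-2.313) = 0.064.

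| SD | Improvement | Dropout split | Last visit | False shift | Type I, formula | Type I, simulated |
|---|---|---|---|---|---|---|
| 7.14 | 4 | 20/20 | T0-T8 | 0 | 5.0% | 5.6% |
| 7.14 | 2.5 | 15/25 | T0-T8 | 0.14 | 5.6% | 5.4% |
| 7.14 | 4 | 15/25 | T0-T8 | 0.22 | 6.4% | 6.0% |
| 7.14 | 4 | 15/25 | T0-T5 | 0.29 | 7.5% | 8.1% |
| 5 | 4 | 15/25 | T0-T5 | 0.29 | 10.1% | 9.3% |
| 7.14 | 2.5 | 10/30 | T0-T8 | 0.28 | 7.3% | 7.7% |
| 7.14 | 4 | 10/30 | T0-T8 | 0.44 | 10.9% | 10.3% |
| 7.14 | 5 | 10/30 | T0-T8 | 0.56 | 14.3% | 13.8% |

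Simulated values are from 4000 runs of LOCF with baseline-adjusted ANCOVA; the simulation error is about 0.3 to 0.5 percentage points. Other runs of the same settings put the fourth row at 6.6-7.4%. Reversing the split reverses the sign of the shift.

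**4. With a true difference of 2.5 points.**
LOCF difference = 2.5 - [dropout in CBT x CBT improvement - dropout in ST x ST improvement] x 0.556. With ST improving 2.5 and CBT 5 points:
- 20%/20%: 2.5 - (1.00 - 0.50) x 0.556 = 2.22
- CBT 30%, ST 10%: 2.5 - (1.50 - 0.25) x 0.556 = 1.81
- CBT 10%, ST 30%: 2.5 - (0.50 - 0.75) x 0.556 = 2.64

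With ST improving 5 and CBT 7.5 points, the two unequal cases become 1.53 and 2.92. LOCF therefore overstates the effect when ST loses more patients. In a simulation of the same unequal-dropout cases (800 runs each), a likelihood estimate from all visits stayed between 2.46 and 2.54, and between -0.02 and 0.02 when there was no true difference.

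**5. Power.** With equal 20% dropout, 2.22/7.14 = ES 0.31, and 165 per arm gives about 80-81% in an unadjusted t-test. If carried-forward values show half of the effect, ES = 0.35 x 0.9 = 0.315 and power is 81%. If they show none of it, ES = 0.35 x 0.8 = 0.28 and power is 72%.

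**The case against.** **Unequal dropout is only an assumption.** The protocol gives no split by arm, and the design works against one: comparable attention in both arms, the same 20 sessions, therapists who deliver both treatments, and interruptions that do not end participation within 9 months. The Primary Endpoint section also says that persistent positive symptoms change very slowly, and LOCF bias shrinks with slow change. This stands as a limit on size. It does not restore the protocol's argument, which is that the bias runs in one direction only.

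**A reader might infer a false-positive rate of 9-10%.** The documents do not support that as the headline. With a 15%/25% split it needs an SD of about 5 and every dropout last seen by T5, whereas the protocol states 7.14 and schedules PANSS at every month through T8.

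**A reader might infer that LOCF makes the stated power wrong.** It does not. The protocol acknowledges the dilution and raises the sample from 130 to 165 per arm for that reason, which roughly covers equal 20% dropout. Power falls clearly short in the equal-dropout case only under the extreme assumption that carried-forward values show no effect at all.

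**A reader might infer a flat contradiction between LOCF and the mixed model.** The Statistical Analysis section does not name time, so it can be read as a single-time-point model at T9. LOCF is then a poor choice, but not an inconsistent one. What stands is that the two sections describe different models.

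**The mixed model also rests on an untestable assumption**, missing at random. True, and a reason for a further sensitivity analysis. LOCF is biased here even when dropout is unrelated to outcome within each arm.

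**Conclusion.** The concern holds in a limited form. LOCF is fixed for the confirmatory test although monthly data make it unnecessary, the two descriptions of the model need reconciling, and the statement that LOCF presumably underestimates the effect is not true in general.

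The size is conditional. With SD 7.14, correlation 0.6, 2.5 to 4 points of improvement and a 15%/25% split, type I error is about 5-7%, with a false shift of roughly 0.15 to 0.3 points; the top of the range, 7-8%, applies if all dropout is early. With SD 5 and early dropout it is about 9-10%. With a 10%/30% split it is about 7-8% at 2.5 points of improvement and 10% or more from 4 points upwards. With equal dropout it is close to 5%. Split, timing, correlation and course of symptoms are all assumptions, and the documents do not show which arm would be favoured.

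**What to change.** 1. State one confirmatory model in both sections: a likelihood-based repeated-measures linear mixed model on all observed PANSS positive scores from T0 to T9, adjusted for baseline and centre, with time in the model and no imputation. The confirmatory test is the treatment contrast at T9.
2. Keep LOCF as a sensitivity analysis and change the Table 3 label to match.
3. Delete the statement that LOCF presumably underestimates the effect. The sample of 165 per arm can stay.
4. Add one sensitivity analysis for data missing not at random, such as shifting the unobserved T9 scores by a range of fixed amounts, separately by arm.

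The cost is wording and some programming; no extra patients or visits are needed. T9 assessments run to October 2010 and the analysis starts in November 2010. The Blinding section withholds the group variable until data checks are complete, so the change can be made and dated before anyone analysing the data sees the allocation.

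### The stated 85% power at an effect size of 0.45 does not follow from the article's own two-group calculation, which gives about 95%

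*Protocol article*

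**What the plan says.** All the relevant figures are in the protocol article, section Sample size calculation. The article explains that it sized the trial as a classical ANOVA because it had no software for the planned mixed model.

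- **Target.** The effect size is 0.35, illustrated by post-treatment PANSS positive scores that "were 12 for CBT and 14.5 for ST with a standard deviation of 7.14".
- **Base case.** "This results in n = 130 per group for a power of 80% and a two-sided significance level of 5" per cent.
- **Dropout.** About 20% is expected, and the number randomised is raised to 330, that is 165 per arm. Table 3 gives 260 patients for the per-protocol analysis, which is 130 per arm.
- **Scenarios.** Low effect: "a reduced ES of 0.2 would result in a power of only 36% for the drop out of 20" per cent. Higher dropout: at 30% dropout and effect size 0.35, power is put at 74%. Favourable effect: "a more favourable ES of 0.45 would increase the power to 85% for the maximum drop-out rate of 20" per cent.

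**The concern.** The scenarios do not fit together. At 20% dropout, moving the effect size from 0.20 to 0.35 is said to raise power from 36% to 80%. A further move to 0.45 is said to add only 5 points. At this sample size the power curve is still climbing steeply at 0.35, so so small a gain is implausible.

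The article says that the literature does not support an assumption about the effect of CBT against ST, and it offers the scenarios for that reason. They are its only statement of power away from an effect size of 0.35. A reader who takes the list at face value would put the chance of missing an effect of 0.45, under the sizing calculation, at 15% instead of about 5%.

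**Working it through.** **Inputs** (all from Sample size calculation)

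- Two groups, 1:1, two-sided 5%.
- Target effect size: (14.5 − 12)/7.14 = 0.350.
- Per arm: 130 in the calculation. After 20% dropout: 165 × 0.8 = 132. After 30% dropout: 165 × 0.7 = 115.5, taken as 115.

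**Formula.** With n per arm and effect size d, the noncentrality is d × √(n/2). By the normal approximation, power ≈ Φ(d√(n/2) − 1.960). The exact figures use the noncentral t distribution on 2n − 2 degrees of freedom.

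**Step 1: reproduce the article's base case.** The n per arm for d = 0.35 and 80% power is 2 × (1.960 + 0.842)² / 0.35², which rounds up to 129. The t distribution gives 130, as stated. Inflation for dropout gives 130/0.8 = 162.5, so 163 per arm; the article plans 165.

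**Step 2: apply the same method to every scenario.** For n = 130, √(130/2) = 8.062.

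| Effect size | n per arm | Normal approximation | Noncentral t | Stated |
|---|---|---|---|---|
| 0.35 | 130 | Φ(2.822 − 1.960) = 80.6% | 80.3% | 80% |
| 0.20 | 130 | Φ(1.612 − 1.960) = 36.4% | 36.2% | 36% |
| 0.35 | 115 | Φ(2.654 − 1.960) = 75.6% | 75.3% | 74% |
| 0.45 | 130 | Φ(3.628 − 1.960) = 95.2% | 95.1% | **85%** |
| 0.45 | 132 | Φ(3.656 − 1.960) = 95.5% | 95.4% | **85%** |

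The first two rows match to the rounded percent, and the third is about one point away. The last two differ from the stated figure by about 10 points.

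**Step 3: ask what 85% would correspond to.** At 130 to 132 per arm, 85% power belongs to an effect size of about 0.37. At an effect size of 0.45 it needs only 90 per arm, which from 165 means 1 − 90/165 = 45% dropout.

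**Step 4: look for a reading that gives 85% and keeps the other figures** (noncentral t).

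- 20% taken off 130 (n = 104): 89.8% at 0.45.
- No loss (n = 165): 98.3%.
- ANOVA error degrees of freedom reduced for six centres: 95.1% at n = 130.
- Effect diluted to 0.8 × 0.45 with all 165 per arm: 90.3%.
- Effect diluted to 0.8 × 0.45 and n cut to 132: 83.0%. The same treatment gives 25% at 0.20 and 62% at 0.35, against the stated 36% and 80%.
- Two-sided 1% instead of 5%: 84.8% at n = 130, but the article fixes 5%, both here and under Statistical Analysis.

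None of these yields 85% under the stated 5% level while leaving the other figures intact.

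**The case against.** The strongest reply is that little depends on the number. It is one illustrative, favourable scenario. The sample size comes from the effect size of 0.35, 80% power, two-sided 5% and 20% dropout, and none of these uses the 85%. The error is conservative and hides no shortfall. Recruitment was already complete when the article was written, so no sizing decision can turn on it. All of this stands, and it makes the point minor. It does not make the number right.

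A second reply concerns what the 95% describes. The confirmatory analysis is by intention to treat on all 330 patients, with last observation carried forward and a mixed model adjusted for baseline and centre. The article itself expects carrying forward to shrink the estimated effect. If dropout diluted 0.45 to 0.36 with all 165 per arm analysed, a two-group test would have about 90% power; baseline adjustment would push the other way. This also stands. A reader might infer that the trial's real risk of missing an effect of 0.45 is 5%, or that the 85% will distort how a null result is read. The documents support neither. The 5% belongs to the simple two-group calculation. The section Lines of interpretation does not draw on power at 0.45, and Statistical Analysis plans to report effects with confidence intervals.

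A misprint for 95% is possible, but nothing in the article shows it.

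**Conclusion.** The point holds as a minor numerical correction. Under the article's own two-group calculation, power at an effect size of 0.45 with 20% dropout is about 95%, not 85%. This rests on 130 to 132 patients per arm, equal allocation and two-sided 5%, all taken from the article, and on the fact that the same method returns its 80% and 36%.

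A reader might also infer that the whole scenario list is unreliable or should be rebased. It should not be: 80% and 36% are right at the article's 130 per arm, and moving to 132 would only shift them to 80.9% and 36.7%. The 74% for 30% dropout is within about one point of the recomputed 75.3% and is not a separate error.

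**What to change.** In Sample size calculation, replace 85% with about 95% for the effect size of 0.45 at 20% dropout. State beside each scenario the number per arm it uses: 130 (or 132) for 20% dropout, and about 115 for 30% dropout, which gives about 75%. Say that these are powers of the two-group calculation used for sizing. The cost is one corrected number and a short clause; the sample size, the analysis and the conduct of the trial are unaffected.
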